#### **9.8.4 Admission of back up volunteers**

To facilitate the timely enrollment of 6 volunteers into the isolation unit at the same time, two additional volunteers may be admitted for each group as back-ups. These back-up volunteers will be admitted to the isolation unit on D-2. If back up volunteers are not needed, then they will be discharged on D0 and all collected samples will be discarded. If another volunteer should withdraw from the study before D0, then the first backup volunteer will act as his or her replacement for the duration of the study. Back up volunteers who are discharged prior to receiving vaccine/placebo are eligible for participation in a future group.

### **9.9 Laboratory evaluations**

The total approximate volume of blood that will be collected from each volunteer is presented in Section 18.7. The total approximate blood volume that will be collected from each household contact is presented in Section 18.8. Total blood volume drawn from each volunteer will not exceed the American Association of Blood Banks (AABB), and US Food and Drug Administration (FDA) guidelines of 550 mL in any eight-week period.

All biological samples must be collected in the appropriate manner. The investigator will ensure that the personnel and laboratory under his/her supervision comply with these requirements. Further details on shipment, handling, and storage of the samples are provided in the Specimen Handling Guidelines.

Any residual samples will be stored indefinitely following completion of the study at the sponsor-designated laboratories. Any future analyses conducted on the samples will maintain volunteer anonymity. Volunteers will have to provide their approval for long-term storage of their biological specimens. Volunteers will have the right to opt out of having their biological specimens stored once all analyses in the Informed Consent Form are completed. Opting out of this procedure does not impact the volunteer's ability to participate in the study.

### **9.10 Potential risks and benefits**

#### **9.10.1 Risks related to vaccines**

Volunteers may exhibit general signs and symptoms associated with the oral administration of a vaccine or placebo. Side effects, if observed, are expected to be short term, mild, and not requiring treatment.

Volunteers may have an allergic reaction to the vaccination. An allergic reaction may cause a rash, hives or even difficulty breathing. Severe reactions are rare. Medications are available in the isolation facility to treat serious allergic reactions.

The effect of this vaccine on a fetus or nursing baby is unknown, as well as the effect on semen. Therefore, sexually active males (unless anatomically sterile) must be willing to use an effective method of contraception (such as consistent condom use) from the day of first vaccination until at least 4 months after vaccination. Female volunteers of child-bearing potential will be required to agree to use birth control for sexual intercourse beginning prior to the vaccination and continuing through the 4 months after vaccination. Women who are pregnant or nursing will be excluded from the study.

The vaccine may cause a positive HIV antibody test using the standard screening test. A positive or indeterminate test may have a negative employment and social impact. As a result, a letter of participation will be provided on request. Volunteers will be discouraged from donating blood during study participation as a result of the potential false-positive HIV antibody test result. If these test results should occur, Western blot analysis, PCR, and/or other required testing will be performed either to exclude or confirm HIV infection. Blood donation options for those volunteers who wish to resume blood donation will be explained at the final study follow-up visit.

#### **9.10.2 Blood draws**

Blood drawing may cause pain, bruising, and, rarely, infection at the site where the blood is taken.

#### **9.10.3 Unknown risks**

There may be other serious risks that are not known. Volunteers may believe that this vaccine provides protection against acquiring HIV infection, and therefore practice riskier behavior. They will receive extensive counseling throughout the study to address this potential problem. It is not known if the study vaccine increases, decreases, or has no effect on the chance of becoming HIV infected when exposed, or if upon becoming HIV infected, the person's disease course progresses faster or slower to AIDS.

#### **9.10.4 Potential benefits**

There is no direct benefit to the volunteer or household contact for participation in this clinical trial. Although study volunteers may benefit from clinical testing and physical examination, they may receive no direct benefit from participation. Society may benefit from knowledge gained in this study that may aid in the development of an HIV vaccine.

## 10 SAFETY ASSESSMENTS

### 10.1 Adverse events

#### 10.1.1 Definitions

##### Adverse events

An AE is any untoward medical occurrence in a patient or volunteer, and does not necessarily have a causal relationship with a medical treatment. This includes any noxious, pathological, or unintended change in anatomical, physiological, or metabolic functions, as indicated by physical signs, symptoms, and/or laboratory-detected changes. These might occur in any phase of the clinical study whether associated with the study vaccine or not. This includes exacerbations of pre-existing conditions or events, intercurrent illness, or vaccine or drug interactions. Anticipated day-to-day fluctuations of pre-existing conditions that do not represent a clinically significant exacerbation are not considered AEs. Discrete episodes of chronic conditions occurring during a study period should be reported as AEs in order to assess changes in frequency or severity.

##### Serious adverse events

Seriousness refers to the outcome of an AE. Seriousness is determined by both the investigator and medical monitor, and can also be determined by the sponsor (*FDA 2010 Guidance for Industry and Investigators; Safety Reporting Requirements for INDs and BA/BE Studies*). An AE or suspected adverse reaction is considered “serious” if, in the view of either the investigator or sponsor, it results in any of the following outcomes:

- Results in **death**.
- Is **life-threatening**: i.e. the volunteer was at risk of death at the time of the event; it does not refer to an event which hypothetically might have caused death if it were more severe.
- Results in persistent or significant **disability/incapacity**: i.e. results in a substantial disruption of the volunteer’s ability to carry out normal life functions. This definition is not intended to include experiences of relatively minor medical significance, such as headache, nausea, vomiting, diarrhea, influenza, infusion site reactions, or accidental trauma (e.g. sprained ankle).
- Requires in-patient **hospitalization** or prolongation of existing hospitalization: i.e. the volunteer is detained (usually at least an overnight stay) at the hospital or emergency ward for treatment that would not have been appropriate in the physician’s office or in an out-patient setting. Hospitalization for either elective surgery related to a pre-existing condition which did not increase in severity or frequency following initiation of the study, or for routine clinical procedures (including hospitalization for ‘social’ reasons) that are not the result of an AE, are **not** considered as SAEs.
- Is a **congenital anomaly or birth defect** in the offspring of a study volunteer
- Is an **important medical event** that may jeopardize the volunteer or may require intervention to prevent one of the other outcomes listed above: e.g. interventions

---

A procedure that may take place during the study period and should not interfere with the study drug administration or any of the ongoing protocol-specific procedures.

such as intensive treatment in an emergency room or at home for allergic bronchospasm; blood dyscrasias or convulsions that do not result in hospitalization, or development of drug dependency or drug abuse. Based on medical and scientific judgment, these events should usually be considered serious.

A suspected transmission of any infectious agent via a medicinal product is always considered as an important medical event, i.e. an SAE.

Although **not** considered as an SAE, cancer should be reported in the same way as SAEs.

Note: If anything untoward is reported during an elective procedure, that occurrence must be reported as an AE, either serious or non-serious according to the criteria defined above.

When in doubt as to whether hospitalization occurred or was necessary, the AE should be considered serious.

### **Adverse reactions**

An adverse reaction is an AE judged to be related to study vaccine.

Related AEs (adverse reactions) are defined as those judged by the investigator, sponsor or independent safety monitor to be possibly, probably, or definitely related to study vaccine.

When an AE is judged to be related to study vaccine and also is judged to be serious and unexpected, it is a SUSAR (suspected unexpected serious adverse reaction) and is volunteer to expedited reporting. All SAEs in this study will be considered unexpected as there are no expected AEs associated with this vaccine product.

Adverse reactions will be reported in accordance with FDA 2009 Guidance for Clinical Investigators, Sponsors and IRBs; Adverse Events Reporting to IRBs – Improving Human Volunteer Protection.

## **10.1.2 Surveillance, reporting, and documentation of adverse events**

The recording of AEs is an essential part of study documentation. The investigator is responsible for documenting all AEs as set out in the following sections.

### **10.1.2.1 Surveillance of adverse events**

At each visit through four months following vaccination, all AEs, either observed by the investigator or one of his/her clinical collaborators, or reported by the volunteers spontaneously or in response to a direct question, will be evaluated by the investigator or designee. All SAEs will be reported through the final visit (Study Day 365).

Volunteers will be instructed to contact the investigator immediately should he/she experience any signs or symptoms he/she perceives as severe from the time of vaccination through a period of 12 months.

#### **10.1.2.2 Documentation of adverse events**

All AEs will be collected on case report forms (CRFs) from the signing of the ICF until Study Day 112. SAEs will be collected through Study Day 365.

AEs and SAEs should be documented in terms of signs and symptoms observed by the investigator or reported by the volunteers. Whenever possible, a medical diagnosis should be made. The nature of each event, date and (where appropriate) time of onset, outcome, severity, and causal relationship should be established. Details of any symptomatic/corrective treatment should be recorded on the appropriate page of the CRF.

Hospitalization for routine clinical procedures (or other reason) that is not the result of an AE, are not considered AEs but will be recorded on the AE page of the CRF ('Hospitalization, Not an AE'). The same applies for hospitalization for elective procedures related to a pre-existing condition that did not increase in severity or frequency during the study. If hospitalization was planned before administration of the study vaccine, it will be documented in the Medical History page of the CRF (see below).

The following events will be documented in the Medical History page of the CRF:

- Pre-existing conditions or signs and/or symptoms present in a volunteer before study start. This includes conditions that were not recognized at study entry but later during the study period.
- Hospitalization arising from a pre-existing condition and planned before the administration of the vaccine.

#### **10.1.2.3 Post-vaccination reactions occurring immediately after each vaccination**

Volunteers will be observed for minimum of 30 minutes following vaccine administration. Vital signs (temperature, blood pressure, pulse and respiratory rate) will be taken and qualified study personnel will evaluate for any signs or symptoms of reactions.

Possible reactions may include fever ( $\geq 37.7$  °C), fatigue/malaise, headache, myalgia, arthralgia, chills, nausea, and vomiting. For life-threatening allergic reactions that occur immediately post-vaccination, the site has specific procedures developed for handling such emergencies.

#### **10.1.2.4 Reactions occurring within ten days (D0-D9) after vaccination**

Volunteers will be housed in an isolation facility for 2 days prior to vaccination (Day -2), for the day of vaccination (Day 0), and for the subsequent 9 days following vaccination (D1-9). The purpose of isolation is to limit the possibility of transmission of the replication-competent viral vector. During the isolation period, study clinicians (MD, NP, or nurse) will visit each volunteer twice daily to monitor vital signs, complete scheduled lab procedures, and assess for any adverse events.

Volunteers will be instructed to notify specified study personnel immediately if any unusual or severe sign or symptom appears after vaccination.

### 10.1.3 SAE Reporting

IAVI has a regulatory obligation to report SAEs to the FDA according to established timetables for reporting based on specific criteria. The investigator will report SAEs to IAVI (or designee) within 24 hours from the time they first learn of the event. The SAE form will be completed as thoroughly as possible and signed by the investigator or his/her designee before transmittal to IAVI (or designee). The investigator will provide his/her assessment of causality to study treatment at the time of the initial SAE report. The investigator will not delay in the reporting of any SAE in order to obtain additional information. Any additional information, if collected, will be reported to IAVI as a follow-up to the initial report.

All SAEs must be reported immediately (within 24 hours of discovery) by email or fax to the sponsor at the following contact information:

Email: [[contact]](mailto:[contact])

[contact]

The Medical Monitor will perform a clinical review of the information provided to identify any missing data. The Medical Monitor will also contact the study site to clarify any discrepant or missing information, to answer questions and to provide guidance to the site, if needed. The investigator will report the SAE as an acceptable medical diagnosis. If a preliminary diagnosis has not yet been made, then each symptom will be listed separately. A follow-up report will be issued when a diagnosis is made.

The investigator must report SAEs to the appropriate IRB as requested by the board according to local legal requirements.

### 10.2 Reporting requirements to the local IRB

The PI/designee will be responsible for providing all safety reports and reporting all SAEs, study pauses, social harms, and major deviations to the local regulatory authorities, such as a local IRB, and any regulatory agencies, in a timely manner according to the institution's guidelines and to local regulations.

### 10.3 Causality assessment of study vaccine to adverse events

Every effort should be made by the investigator to explain any AE and assess its potential causal relationship, i.e. to administration of the study treatment or to alternative causes (e.g. natural history of the underlying diseases, concomitant therapy). This applies to all AEs, whether serious or non-serious.

The investigator will use the following guidelines to assess the causal relationship of an AE to study injection:

- |                                       |                                                                                                                                                                   |
|---------------------------------------|-------------------------------------------------------------------------------------------------------------------------------------------------------------------|
| Not related:                   | Adverse experiences felt to be due to extraneous causes that neither follows a known pattern of response nor a reasonable temporal relationship to study vaccine. |
| Remote (probably not related): | Adverse experiences that are unlikely to be related to study vaccine but which follow a reasonable temporal relationship,                                         |

such that this cannot be completely excluded or events that could be associated with study vaccine but which are unrelated in time.

**Possibly related:** Adverse experiences that may be due to extraneous causes but which follow a known pattern of response and/or a reasonable temporal relationship to study vaccine.

**Probably related:** Adverse experiences that cannot be explained by extraneous causes; which follow a known pattern of response and/or a reasonable temporal relationship; which disappear or decrease on cessation of study vaccine and reappear on re-challenge.

**Definitely related:** Adverse experiences that have a definite relationship to the study vaccine (e.g. anaphylactic reaction after vaccination) without any other explained causes; which follow a known pattern of response and/or a reasonable temporal relationship; which disappear or decrease on cessation of study vaccine and reappear on re-challenge.

In the final analyses, events categorized as “not related” and “remote” will be considered as not related to study vaccine; events categorized as “possibly related”, “probably related” and “definitely related” will be considered as related to study vaccine.

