**Table 2: AE notification and safety pause/AE review rules**

| Event and relationship to study product                                                                                      | Severity                  | Occurrence          | Site PI action                                               | PSRT or SMC action                                   |
|------------------------------------------------------------------------------------------------------------------------------|---------------------------|---------------------|--------------------------------------------------------------|------------------------------------------------------|
| SAE, related                                                                                                     | Any                       | Any                 | Phone, email or fax forms to sponsor within 24 hours         | Study pause within 24 hours, refer to SMC for review |
| SAE, not related                                                                                                 | Grade 5                   | Any                 | Phone, email or fax forms to sponsor within 24 hours         | PSRT review within 2 business days to consider pause |
| AE  , related                                                                                        | Grade 3 or 4  | Second  | Phone, email or fax notification to sponsor within 24 hours  | Study pause within 24 hours, refer to SMC for review |
| AE  , related                                                                                        | Grade 3 or 4  | First               | Phone, email or fax notification to sponsor within 24 hours  | PSRT review within 2 business days to consider pause |
| Documented VISR in household contact                                                                                         | N/A                       | Any                 | Phone, e-mail or fax notification to sponsor within 24 hours | Study pause within 24 hours, refer to SMC for review |
| Documented illness compatible with Ad26 infection associated with a positive Ad26 serology in household contact  | N/A                       | Any                 | Phone, email or fax forms to sponsor within 24 hours         | Study pause within 24 hours, refer to SMC for review |

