 Related SAE refers to SAE deemed to be definitely, probably, or possibly related to study vaccine.

 Not related SAE refers to SAE deemed to be probably not related or not related to the study vaccine.

 Does not include the following reactogenicity symptoms (fatigue/malaise, myalgia, arthralgia, chills, headache, nausea, vomiting).

 Related AE refers to fever, conjunctivitis, gastroenteritis, cystitis, upper respiratory infection, or other AE that is judged probably or definitely related to the vaccine.

 If no evidence of disease is present other than an abnormal laboratory value, the test must be repeated (entailing blood re-draw) at least one time. The verification period will be a maximum of 72 hours after initial awareness of the abnormal laboratory value. When signs and symptoms are present, repeat test will not be needed.

 PSRT will determine whether the reported related AE (Grade 3 or 4) is a second occurrence of a previously reported AE (Grade 3 or 4).

 "Positive Ad26 serology" means a \*newly\* positive Ad26 serology compared to enrollment that develops \*after\* a documented illness compatible with Ad26 infection in a household contact.

For events in the table above, the Site Principal Investigator (PI) notifies the IAVI Medical Monitor (within a few hours after the site observes, or is notified of, the AE) and the IAVI Medical Monitor then notifies the PSRT immediately (within 24 hours). The PSRT will convene within two business days to review these AEs. The PSRT will review and determine disposition (including whether the SMC needs to review the event).

If a study pause is triggered, all enrollment and vaccinations will be held until review by the SMC. Resumption of enrollment and study treatment may be determined by the SMC (in consultation with the FDA, if required) following a cumulative review of the available safety data. If a decision to resume study enrollment and study treatment

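### Section 10.3 ties the two top causality grades to a re-challenge that a one-dose trial cannot give; read literally, the Grade 3/4 related-AE rows of Table 2 miss non-serious events outside five named conditions

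*Protocol*

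**What the plan says.** Section 10.3 grades causality on five levels, which the investigator is to use as guidelines. The two highest, *probably related* and *definitely related*, both end with the requirement "which disappear or decrease on cessation of study vaccine and reappear on re-challenge". Neither carries a qualifier for cases where re-challenge does not arise. The overview, the objectives and Section 18.5 all give a single oral administration, on Day 0.

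Table 2 in Section 9.8.3 has two rows for related Grade 3 or 4 AEs. At the first event the action is "PSRT review within 2 business days to consider pause"; at the second it is a study pause within 24 hours and referral to the SMC. Both rows require the site to notify the sponsor within 24 hours. Footnote 4 defines relatedness for these rows: "Related AE refers to fever, conjunctivitis, gastroenteritis, cystitis, upper respiratory infection, or other AE that is judged probably or definitely related to the vaccine". Footnote 5 adds a condition for laboratory findings: "If no evidence of disease is present other than an abnormal laboratory value, the test must be repeated". Footnote 3 removes seven symptoms from these rows: "Does not include the following reactogenicity symptoms".

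Elsewhere relatedness is wider. Footnote 1 says "Related SAE refers to SAE deemed to be definitely, probably, or possibly related to study vaccine". Related AEs in Section 10.1.1 "are defined as those judged by the investigator, sponsor or independent safety monitor to be possibly, probably, or definitely related to study vaccine". In the final analyses, Section 10.3 states that events graded possibly, probably or definitely related "will be considered as related to study vaccine".

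**The concern.** A causality grade that nobody can receive is normally a drafting blemish. Here a stated pause rule depends on it. If the two upper grades are out of reach, the part of footnote 4 that admits AEs beyond the five named conditions is empty.

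Three fixed actions would then be lost for those events: notification within 24 hours, PSRT review at the first event and the automatic pause at the second. Section 9.5 links dose advancement to the same table: if no pausing criterion is met, the next group is enrolled. The rule carries weight because Section 3.1.3 reports no formal toxicology study of this replicating vector, and Section 4.3 says the insert had not previously been tested in humans.

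**Working it through.** The protocol states no figure on this point, so the check sets the provisions side by side and then counts the scheduled assessments affected.

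**1. Can the criterion be met?** Each volunteer receives 1 dose and no second dose is scheduled, so re-challenge is available to 0 of 24 volunteers. Household contacts, to whom Section 9.8.3 also applies the table, receive none. The requirement joins cessation and re-challenge with *and*, so resolution of the event alone does not satisfy it.

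**2. Highest grade reachable.** 2 of the 5 grades carry the clause. Without them the ceiling is *possibly related*.

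**3. Where does that ceiling matter?**

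| Provision | Includes *possibly*? | Affected? |
|---|---|---|
| Table 2 footnote 1, related SAE | Yes | No |
| Section 10.1.1, adverse reactions | Yes | No |
| Section 10.3, final analyses | Yes | No |
| Table 2 footnote 4, related Grade 3/4 AE | No | Yes, outside the five named conditions |

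Footnote 4 governs 2 of the 6 rows of Table 2.

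**4. Which events fall in the gap?** Non-serious Grade 3/4 events that are neither one of the five named conditions nor one of the seven symptoms in footnote 3. Examples from the grading table in Section 18.1 are ALT or AST at 5.1 to 10.0 x ULN, creatinine at 1.9 to 3.4 x ULN, and generalized urticaria (Grade 3). None of the five named conditions is a laboratory abnormality. Footnote 5 can therefore operate only through the part of footnote 4 that the clause empties, which shows that the rows were meant to reach laboratory values.

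**5. How many scheduled laboratory panels are concerned?** AEs are collected to Day 112 (Section 10.1.2.2). Post-dose blood count and chemistry draws up to then are on Days 7, 17 and 112 (Sections 18.5 and 18.7).

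- All panels: 24 x 3 = 72; vaccinees 20 x 3 = 60.
- Less Group 4, where a pause protects no later group: 6 x 3 = 18; vaccinees 5 x 3 = 15.
- Less Day 7 in Groups 1 to 3, inside the D0-D9 data that the SMC reviews before escalation: 6 x 1 x 3 = 18; vaccinees 5 x 1 x 3 = 15.
- Remaining: 72 - 18 - 18 = 36; vaccinees 60 - 15 - 15 = 30. Check: 6 x 2 x 3 = 36 and 5 x 2 x 3 = 30.

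The 36 is an upper limit. A Day 17 or Day 112 result protects a later group only if that group is still undosed. Groups may follow one another after as little as 9 days of observation, and enrollment is expected to finish within 6 months. These are counts of assessments, not expected events.

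**The case against.** The strongest reply is that nobody would apply the clause. The scale is offered as guidelines, its own example of a definite relation is anaphylaxis (which is not re-challenged), and footnote 5 presupposes that laboratory events reach these rows. This stands as evidence that the wording was carried over without adaptation and that an intended exclusion is unlikely. It does not repair the text: two assessors could grade the same event differently, and the grade decides whether a row fires.

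Second, footnote 4 names no judge, and Section 10.1.1 lets the sponsor or an independent safety monitor judge relatedness as well. That leaves some room. But Section 10.3.1 has the investigators determine relation to vaccine, and the protocol offers no other scale for the pause rules.

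Third, other safeguards remain: the related-SAE row includes *possibly*; the SMC reviews available data before each escalation (Sections 9.5 and 10.9); ad hoc review (Section 6.4) and suspension at the discretion of the PI or PSRT (Section 9.8.3) are open; and AE forms are entered in real time (Section 10.3.1). These narrow the gap, but they are not the fixed actions of the table.

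Stronger readings are tempting and go too far:

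- A reader might infer that the Grade 3/4 rows are disabled altogether. Footnote 4 lists five conditions by name and most naturally attaches the causality judgement to other AEs only, so those five still trigger.
- A reader might count all 72 panels (60 in vaccinees) as unprotected. Step 5 shows why half of them do not belong.
- A reader might infer that related events will be under-reported. The final analyses count *possibly related* events as related.
- A reader might expect the wording change to bring every laboratory rise into the rows. A rise with a plausible other cause would remain *possibly related*, which footnote 4 leaves out.

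**Conclusion.** The point holds as a defect of wording that sits under a stated pause rule. Applied literally, the causality scale stops 2 of the 6 rows of Table 2 from firing for non-serious Grade 3/4 events outside the five named conditions, against the evident purpose of footnote 5. The practical effect depends on the investigator following the clause to the letter; one who disregards it closes the gap. On scheduled laboratory work the exposure is at most 36 panels, 30 of them in vaccinees; clinical events such as urticaria are additional and cannot be counted in advance. The documents give no event rate, so neither a probability of a missed pause nor an expected number of missed events can be stated. The point should be corrected because the pause rule is explicit and the correction is small, but the documents do not show that the trial lacks safety oversight.

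**What to change.** In Section 10.3, delete the cessation and re-challenge clause from both *probably related* and *definitely related*, or add a where-applicable qualifier to each. The grades then rest on alternative causes, pattern of response and timing, and both become reachable. Table 2 need not change: leaving *possibly related* events out of footnote 4 can remain as a deliberate threshold if the sponsor wants it. The cost is a wording amendment to two definitions and a short note to the site on grading. The downside is that a few more events reach PSRT or SMC review.
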